## Follow-up of adverse events

All adverse events will be followed until they have abated, or until a stable situation has been reached. Depending on the event, follow up may require additional tests or medical procedures as indicated, and/or referral to the general physician or a medical specialist.

## Data Safety Monitoring Board (DSMB)

The Data Safety Monitoring Committee of the Dutch Obstetrical Consortium has been approached to monitor the progress of the study and safety of participating women. This committee consists of prof. dr. [name] (clinical epidemiologist AMC), prof. dr. [name] (neonatologist AMC) and prof. dr. [name] (gynecologist LUMC)

Serious adverse events (SAE) will be reported directly to this committee.

The advice(s) of the DSMB will be notified upon receipt by the sponsor to the METC that approved the protocol. With this notification a statement will be included indicating whether the advice will be followed.

# STATISTICAL ANALYSIS

## Descriptive statistics

- 1. Maternal age: continuous, quantitative
  2. ASA physical status: continuous, quantative (1-5)
  3. Body Mass Index: continuous, quantative
  4. Parity: categorical, quantitative: (nulliparous / multiparous)
  5. Previous cesarean delivery: categorical, quantitative (yes/no)
  6. Gestational age: continuous, quantitative
  7. Maternal origin: categorical, quantitative (Caucasian, Mediterranean, Creole, Asian)
  8. Educational level: categorical, quantitative
  9. Number of fetuses: categorical, quantitative (1-3)
  10. Fetal condition at time of request pain relief: categorical, quantitative (optimal, non reassuring, fetal tachycardia)
  11. Start of labor: categorical, quantitative (spontaneous/induction)
  12. Use of oxytocin: categorical, quantitative (yes/no)

Mode of delivery: categorical, quantitative (vaginal delivery, instrumental delivery,

cesarean section)

- 1. Indication for cesarean section/ instrumental delivery: categorical, quantitative Duration first stage of labor: continuous, quantitative
  2. Duration second stage of labor: continuous, quantitative
  3. Time from request to start of analgesia: continuous, quantitative
  4. Duration of analgesia: continuous, quantitative
  5. Conversion from epidural analgesia to RPCA: categorical, quantitative (yes/no)
  6. Conversion from RPCA to epidural analgesia: categorical, quantitative (yes/no)
  7. Type of medication used for epidural analgesia: categorical, quantitative
  8. Increases or decreases in bolus dose for RPCA: categorical, quantitative
  9. Maternal pain scores: continuous, quantitative (0-10)
  10. Maternal pain appreciation scores: continuous, quantitative (0-10)
  11. Maternal satisfaction with analgesia: continuous, quantitative (0-10)
  12. Maternal temperature: continuous, quantitative
  13. Start of intravenous broad spectrum antibiotics; quantitative (yes/no)
  14. Maternal saturation: continuous, quantitative
  15. Maternal respiratory depression: categorical, quantitative (yes/no)
  16. Oxygen administered: categorical, quantitative (yes/no)
  17. Maternal hypotension: categorical, quantitative (yes/no)
  18. Nausea/vomiting: categorical, quantitative (mild, moderate, severe)
  19. Itching: categorical, quantitative (mild, moderate, severe)
  20. Postpartum hemorrhage >1000 ml: categorical, quantitative (yes/no)
  21. Major maternal complication
  22. Post spinal headache: categorical, quantitative (yes/no)
  23. Apgar 1 and 5 minutes: continuous, quantitative
  24. Arterial umbilical cord pH: continuous, quantitative
  25. Admission to neonatal ward: categorical, quantitative (yes/no)
  26. Number of visits to/from primary health care mother: continuous, quantitative
  27. Number of visits to/from primary health care child: continuous, quantitative
  28. Number of visits to/from gynecologist: continuous, quantitative
  29. Number of visits to/from pediatrician: continuous, quantitative
  30. Duration of neonatal admission: continuous, quantitative

Duration of maternal admission: continuous, quantitative

We will report on the primary outcome measure, pain appreciation, as area under the pain appreciation curve (AUC), this as a measure for the aggregate effect of pain appreciation over a period of time (27). Total pain relief (TOTPAR) is a time weighted measure of AUC or total area under the pain appreciation curve and is a summary measure that integrates serial assessments of a subject’s pain appreciation over the duration of the study. The AUC will be analyzed from the start of active labor and for the whole duration of labor. We will also perform analysis from start of pain relief for the duration the pain relief is given. Subgroup analysis is planned for the AUC for 0-4 hours, 4-8 hours and >8 hours after the start of pain relief.

The trial is designed as an equivalence trial in which the null hypothesis

is that the difference in pain appreciation score between the two treatment groups is

greater than 10%. Preliminary data in perioperative patients on PCA opioid treatment show that changes (i.e. increases) in pain score of 10% or larger will prompt an action of the patient (i.e. she will require additional pain relief by pressing the PCA button). Extrapolating these data to the current study suggests that at VAS score differences of 10% or greater clinical differences in pain appreciation may be assumed.

The analysis of the randomised clinical trial will be by intention to treat, stratified for

centre and parity. First, the epidural and remifentanil group will be compared. Relative risks and 95% confidence intervals will be calculated for the relevant outcome measures. Categorical variables will be tested with the Chi-square test or Fisher’s exact test. Continuous variables will be tested with the Mann-Whitney U test. Time to delivery will be assessed using Kaplan-Meier analysis. Pain scores will be analyzed separately. We will report on pain during labor (area under the curve and mean pain score), worst pain during labor, pain scores at request pain relief. The analysis will be repeated on a par protocol basis. Subsequently, planned subgroup analysis will be done for nulliparous versus parous women, previous caesarean section, preterm labor (32 to 34 weeks and 34-37 weeks) and term labor (37-42 weeks), spontaneous versus induced labor, maternal educational level, maternal age (under 35 years versus over 35 years), multiple pregnancy. We will then use decision analysis to evaluate which intervention strategy, ie epidural analgesia or remifentanil is preferred in women who need analgesia during labor.

The low risk women will be included and analyzed in a separate trial. In the Dutch system with midwifery care and home births, there might be a difference in expectation of women with regard to pain during labor.

To be able to convince both primary and secondary care providers, these groups will be analyzed separately.

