Recently a new opioid, remifentanil, was introduced. Remifentanil, is a new synthetic opioid (anilidopiperidine) with direct agonist action specifically on µ-opioid receptors (6). The rapid onset and offset of the drug make remifentanil very suitable for administration via patient controlled analgesia (PCA), which can be used for analgesia during labor. Placental transfer of remifentanil does occur but appears to be rapidly metabolized, redistributed, or both. There were no adverse neonatal or maternal effects, only mild maternal sedation and respiratory changes (7). There have been multiple clinical studies on the use of remifentanil in the parturient (8-20).

A recent randomized study that compared RPCA with EA showed that in terms of pain scores (pain-intensity), EA is superior to that provided by RPCA. However, there was no difference in the pain appreciation scores between the treatments (21).

These findings were confirmed in our own pilot study that compared pain and pain appreciation scores in 20 women, randomized for RPCA or EA.

In our unpublished data (pilot study and STER study), 100 women received RPCA and only in one case medication had to be stopped because of serious side-effects (decrease in respiratory rate).

We hypothesize that RPCA is as effective in improving pain appreciation scores as EA, with lower costs and easier achievement of 24 hours availability of pain relief for women in labor.

Since we know from other studies that equality in pain appreciation scores can be anticipated, this study will, next to pain appreciation, also investigate patient satisfaction and costs. In this study patients receiving PCA remifentanil will titrate themselves to an acceptable level of pain relief by pressing a button (and receiving an analgesic bolus dose).

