## Study procedures

Women will be asked to participate in this study before active labor has started, preferably during antenatal consult in the third trimester. They will be randomized and allocated to one of the treatment groups. If they request pain relief during labor they will be treated according to randomization with:

1. Remifentanil patient controlled analgesia; 30 microgram boluses, lockout time 3 minutes, maximum dose limit 1200 microgram/hour. Possibility of increasing or decreasing the bolus dose. When indicated EA is available.

2. Epidural analgesia; according to local protocol. When indicated RPCA is available.

There will be no additional invasive tests performed. Maternal vital parameters (temperature, heart rate, blood pressure, respiratory rate and pulse oxymetry) will be monitored non invasively at regular intervals. In the first hour after starting pain relief these parameters will be monitored with intervals of no longer than 15 minutes, after that with intervals of no longer than 1 hour. Maternal pulse oxymetry will also be monitored continuously.

Fetal heart rate and uterine activity will be measured continuously by external monitoring. When data are difficult to interpret or complications (such as meconium stained amniotic fluid, failure to progress in labor) occur, invasive monitoring by means of scalp electrode and intra-uterine pressure recording can be instituted.

Observations for known side effects will be made; respiratory depression, hypotension, nausea/vomiting and itching. Side effects will be managed by established local protocols.

Hypotension (systolic blood pressure < 90 mmHg or > 25% below baseline) will be treated with intravenous fluids, ephedrine 5 mg i.v. or phenylephrine 0.1 mg i.v. When oxygen saturation drops below 92% oxygen will be given.

Maternal pain score and pain appreciation score will be assessed using a visual analogue scale (VAS) ranging from 0-10. Women will be asked to mark the level of pain experienced during a contraction every hour starting at admission in the delivery room. Pain appreciation scores will be asked every hour, participating women will be asked to mark their level of satisfaction with analgesia. This will also be assessed using the visual analogue scale ranging from 0-10. After delivery an overall satisfaction score with pain(0-10) will be asked. Patient satisfaction will also be assessed by HADS and WDQ.

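### Section 8.1 sends the wait from request to analgesia to Mann-Whitney, where a woman who delivers before any analgesia starts has no value; leaving such women out would understate the wait in the slower arm (minor)

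*Protocol*

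**What the plan says.** Three statements in protocol section 8.1 (Descriptive statistics) fix how this variable is handled.

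- The variable list contains "Time from request to start of analgesia: continuous, quantitative".
- The analysis text gives one rule for all such variables: "Continuous variables will be tested with the Mann-Whitney U test".
- The next sentence names a time-to-event method for one other variable only: "Time to delivery will be assessed using Kaplan-Meier analysis".

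The same section sets the analysis population: "The analysis of the randomised clinical trial will be by intention to treat, stratified for" centre and parity. It adds: "The analysis will be repeated on a par protocol basis".

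Section 6.3 (Study procedures) makes the request the start of the clock: "If they request pain relief during labor they will be treated according to randomization with" the allocated method. For the epidural arm it adds: "Epidural analgesia; according to local protocol. When indicated RPCA is available".

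The Introduction expects RPCA to match EA on pain appreciation "with lower costs and easier achievement of 24 hours availability of pain relief for women in labor".

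No section says how a woman who requests relief but never starts analgesia is counted in the waiting-time comparison.

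**The concern.** Time from request to start is an event time that delivery can cut off. A woman who delivers first has a request time but no start time, so a rank test on a continuous variable has no value for her. Intention to treat settles which arm she belongs to, but not what value she gets.

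With no rule, the simplest course at analysis is to drop her. A long wait is more likely to be overtaken by delivery than a short one, so dropping these women removes mostly long waits, and more of them in the slower arm. The protocol itself suggests that this is EA: the Introduction blames logistics for poor access to EA and says that RPCA does not need an anesthetist present. The error would therefore make EA look faster than it is and narrow the gap to RPCA.

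What is at stake is one descriptive result. It is, however, the only listed variable that measures how soon relief follows a request, and easier availability is part of the stated rationale for RPCA.

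**Working it through.** **Figures in the plan.** The protocol gives none for this variable: no expected wait, no time from request to delivery and no share of requesters left untreated. Its sample size (section 4.4) concerns pain appreciation and reproduces exactly:

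- per group: 2 × 2.2² × (1.960 + 1.282)² / 1² = 101.7, rounded up to 102;
- after cross-over: 102 / (1 − 0.10 − 0.30)² = 283.3, rounded up to 284 per arm, or 568 in total;
- randomised: 568 / 0.5 = 1136.

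None of this depends on the waiting time.

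**Model (all inputs assumed).** Let W be the wait that would occur if delivery did not intervene, and D the time from request to delivery. W is observed only if W < D.

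- W and D are independent and lognormal, with log-SD 0.6 and 0.8.
- Median W is 15 min for RPCA and 30, 60 or 90 min for EA.
- Median D is 120, 180 or 300 min in both arms.
- 1,000,000 draws per arm and setting.

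Three EA medians are compared: the underlying one (W), the one among treated women (W given W < D), and the one over all requesters with never-started women ranked longest.

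| Median D (min) | EA never started | EA median, underlying | EA median, treated only | Shortfall | EA median, all requesters | EA−RPCA, underlying → treated only |
|---|---|---|---|---|---|---|
| 300 | 1.1% | 30.0 | 29.8 | 0.2 | 30.0 | 15.0 → 14.8 |
| 300 | 5.4% | 60.0 | 57.9 | 2.1 | 60.4 | 45.0 → 42.9 |
| 300 | 11.4% | 90.0 | 83.9 | 6.1 | 91.9 | 75.0 → 68.9 |
| 180 | 3.7% | 30.0 | 29.2 | 0.8 | 30.1 | 15.0 → 14.3 |
| 180 | 13.6% | 59.9 | 55.1 | 4.8 | 61.6 | 44.9 → 40.2 |
| 180 | 24.5% | 90.1 | 78.2 | 11.9 | 98.2 | 75.1 → 63.2 |
| 120 | 8.3% | 30.0 | 28.5 | 1.5 | 30.4 | 15.0 → 13.7 |
| 120 | 24.4% | 60.0 | 52.1 | 7.9 | 65.3 | 45.0 → 37.3 |
| 120 | 38.6% | 90.0 | 72.4 | 17.6 | 116.1 | 75.0 → 57.6 |

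In the RPCA arm 0.1% to 1.9% never start, and the median moves by at most 0.2 min. With the plan's 284 requesters per arm, the EA arm would lose from about 3 women (284 × 0.011) through 39 (284 × 0.136) to 110 (284 × 0.386).

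**Effect on the named test.** Mann-Whitney compares P(EA wait > RPCA wait). Restricting to treated women moves it from 0.948 to 0.944 in the middle case (EA 60 min, D 180 min). The largest change in any setting is from 0.949 to 0.939.

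**Second model.** With D gamma (shape 1.5), W lognormal (log-SD 0.6) and an RPCA median of 20 min, the direction is the same:

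- EA 60 min, mean D 4 h: 17% of EA and 4% of RPCA requesters never start; treated-only EA median 55 min, a shortfall of 60 − 55 = 5 min.
- EA 60 min, mean D 2 h: 36% of EA requesters never start; 51 min, a shortfall of 9 min.
- EA 90 min, mean D 4 h: 27% of EA requesters never start; 79 min, a shortfall of 11 min.

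**The case against.** The strongest reply is that the protocol nowhere restricts this variable to women who received analgesia. It names intention to treat, it does not forbid ranking non-starters last within Mann-Whitney, and the SAP, which is not available here, may contain a rule. This stands in part: exclusion is what the stated method yields when no rule is given, but the protocol does not state it. What remains is that the protocol goes beyond silence. It assigns this variable a method that needs an observed value and keeps the time-to-event method for another variable.

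Four further points limit the matter, and all stand:

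- Waiting time is not among the objectives (section 2) or the endpoints (sections 6.1.1 and 6.1.2). It is one line in a long list.
- The variable is the start of analgesia, not of the epidural. An EA-allocated woman given RPCA may have a start time, so the EA never-started shares above may be too high.
- The Introduction says that the participating hospitals can already offer an epidural round the clock. Waits there say little about the national access problem, however they are analysed.
- The size rests wholly on assumed waits.

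A reader might also infer a larger error by setting the treated-only median against the median over all requesters. In the second model that means 55 against 64, 51 against 76 and 79 against 103 min. Those larger figures combine waiting with never being treated, so the gap is not the amount by which the wait itself is understated.

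**Conclusion.** The point holds as a minor one. Section 8.1 gives this event time a method under which a woman who delivers before any analgesia starts has no value. If such women are left out, the reported wait in the slower arm and the EA−RPCA difference are biased downward. Under the assumed inputs the EA median is understated by 0.2 to 17.6 min, and by about 5 min in the middle case.

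The direction rests on longer waits being cut off by delivery more often, and on EA being the slower arm. The size cannot be derived from the protocol.

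Two stronger readings are not supported. One is that the protocol plans to analyse only women who received analgesia; no section says so. The other is that the treatment comparison or the trial's conclusion is compromised: the rank comparison hardly changes, and the pain appreciation analysis and the sample size do not use this variable.

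**What to change.** In section 8.1 or the SAP:

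1. Define the population for this variable as all women who request pain relief, in their allocated arm.
2. Report by arm the cumulative incidence of analgesia start after request, with delivery before start as competing event. Do this once for any method and once for the allocated method, so that EA women given RPCA are visible.
3. If Mann-Whitney is kept, rank women who never started as the longest wait.
4. Report the number per arm who requested but never started.

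These summaries describe the share of requesters who have relief by a given time. They do not estimate the underlying wait, and the text should say so.

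The cost is a few sentences and a little extra analysis. The times needed are implied by analyses already planned (pain at request, duration of analgesia, time to delivery), provided that a request is recorded even when no analgesia follows.

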## Sample size calculation

The initial analysis will be performed by intention to treat. We hypothesize that there is no difference in pain appreciation scores with the two sided test, an alpha of 0.05 and 90% power. In this equivalence design in each group 102 women have to be treated to exclude a potential clinical relevant difference of 10% (10 point scale, estimated SD 2.2). Allowing for 10% and 30 % cross-over/ non-compliance in the control group and experimental group respectively, 568 patients are required. When only 50 percent of all women need actually treatment 1136 women have to be randomized. We estimate that in the group of pregnant women who are willing to participate in the study 50% will actually need pain relief. This in contrast to the general Dutch pregnant population, which is known for a low uptake of pain relief during labor.

**4.4.1** Sample size for population of low risk pregnant women.

We hypothesize that there is no difference in pain appreciation scores with the two sided test, an alpha of 0.05 and 90% power. In this equivalence design in each group 102 women have to be treated to exclude a potential clinical relevant difference of 10% (10 point scale, estimated SD 2.2).

We estimate that in the group of pregnant women who are willing to participate in the study 50% actually need pain relief. Therefore 408 women have to be randomized.

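### The primary analysis set and time window do not match the sample size and, read literally, dilute the difference towards equivalence

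*Protocol*

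**What the plan says.** All references are to the protocol; no SAP is at hand.

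- **Window (8.1).** "The AUC will be analyzed from the start of active labor and for the whole duration of labor". A second window is added: "We will also perform analysis from start of pain relief for the duration the pain relief is given".
- **Principle (8.1).** "The analysis of the randomised clinical trial will be by intention to treat, stratified for" centre and parity. No restriction to women who asked for analgesia is stated. A per-protocol repeat is planned.
- **Who is randomised (sections 1 and 6.3).** Women are allocated before active labour and treated only on request or for a medical reason. Section 4.3 lists reasons for withdrawal after randomisation; not requesting analgesia is not among them.
- **What is measured (6.1.1).** Pain appreciation is scored hourly from the start of labour, so untreated women also yield a curve.
- **Sample size (4.4).** The calculation counts treated women: "in each group 102 women have to be treated". It then adds "Allowing for 10% and 30 % cross-over/ non-compliance in the control group and experimental group respectively, 568 patients are required", and finally "When only 50 percent of all women need actually treatment 1136 women have to be randomized".
- **Objective (Summary).** The target is women who request pain relief in labour.

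**The concern.** Sections 4.4 and 8.1 describe different comparisons. Section 4.4 sizes a comparison among women who receive analgesia. Section 8.1, taken at its word, compares everyone randomised over the whole of active labour. In a superiority trial, adding untreated women and untreated hours would cost power. In an equivalence trial it helps the claim: the expected difference shrinks, the margin stays where it was, and the larger number narrows the interval.

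The margin itself is extrapolated from patients using PCA opioids (sections 1 and 8.1), so it was not chosen for a population of whom half receive nothing. More than one endpoint depends on this, because section 6.1.2 makes the cost comparison conditional on equivalence in pain appreciation.

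**Working it through.** **Inputs from section 4.4.** The test is "with the two sided test, an alpha of 0.05 and 90% power"; the aim is to "exclude a potential clinical relevant difference of 10% (10 point scale, estimated SD 2.2". I read 10% as 1.0 point. Expected uptake is 50%, and cross-over is 10% and 30%.

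**Reproducing the plan's figures**
- Treated women per arm: 2 × (1.960 + 1.282)² × 2.2² / 1.0² = 101.7, so 102.
- Cross-over: 102 / (1 − 0.10 − 0.30)² = 102 / 0.36 = 283.3, so 284 per arm and 568 in total.
- Untreated women: 568 / 0.5 = 1136.

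All three agree with the protocol. The two adjustments differ in kind. Cross-over is squared, as a dilution of the effect should be. Non-use is a single division, which only replaces women who drop out of the comparison. Had the untreated women been meant to stay in, the same logic would give 102 / (0.6 × 0.5)² = 1133.3 per arm, about 2267 in total.

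**False equivalence on the literal reading**

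With 568 per arm, SE = 2.2 × √(2/568) = 0.1305. Equivalence is declared if the estimate lies within ±(1.0 − 1.96 × 0.1305) = ±0.744. For a true difference d in treated women and dilution factor f, the probability is Φ((0.744 − f·d) / 0.1305); the opposite tail is negligible.

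| d in treated women | f = 0.5 (half untreated) | f = 0.5 × 0.6 = 0.3 (with cross-over) |
|---|---|---|
| 1.0 | 0.969 | > 0.999 |
| 1.5 | 0.482 | 0.988 |
| 2.0 | 0.025 | 0.865 |
| 3.0 | about 0 | 0.116 |

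The nominal rate at d = 1.0 is 0.025.

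**Sensitivity at d = 1.0, f = 0.5**
- 90% instead of 95% CI: 0.986.
- SD 3.0 in the mixed population (assumption): SE = 0.178, limit 0.651, probability about 0.80.
- Low-risk women analysed separately. Section 4.4.1 gives them 408, and the text does not settle whether they are part of the 1136. If they are, (1136 − 408) / 2 = 364 per arm, SE = 0.163, limit 0.680, probability about 0.87.

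**Requesters only**

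With 284 per arm, SE = 0.1846 and the limit is 0.638. At d = 1.0 without cross-over the rate is 0.025. With the planned cross-over the expected difference is 0.6, and Φ((0.638 − 0.6) / 0.1846) = 0.58. Restricting the set therefore removes one source of dilution and leaves the other.

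**The case against.** **The set is inferred.** No sentence in the protocol says that untreated women are in the primary analysis set. Intention to treat implies it, but the objective, the sample size and the decision analysis in 8.1 all point to women who need or request analgesia. Exact set definitions are often left to a SAP. This stands, so the firm finding is a conflict between sections. It does not dispose of the point. On the requesters-only reading the stated window still includes the hours before analgesia. If 20% to 33% of active labour precedes it (assumption), a difference at the margin passes about 19% to 44% of the time with 284 per arm, before any cross-over.

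**Safeguards exist.** An AUC over the analgesia period, AUCs for three periods after its start, and a per-protocol repeat are all planned. They lessen the problem, but none is made a condition for claiming equivalence. A woman who never asks has not departed from the protocol, so a per-protocol set need not exclude her.

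**Untreated women may differ between arms.** A reader might infer that the arms are identical before or without analgesia. The documents do not support that: allocation is open (6.2) and women know their assigned method before labour (section 1), which can affect both satisfaction and the decision to ask. The factor 0.5 is therefore an assumption.

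**All-randomised is a legitimate question.** The Summary frames RPCA as a first-choice strategy, and an all-randomised comparison answers that. It would, however, need a margin and a sample size made for it.

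**Conclusion.** The concern holds as a conflict between sections with a predictable direction. Taken literally, section 8.1 at least roughly halves the difference that section 4.4 was sized to examine, keeps the margin, and so favours equivalence. A difference equal to the margin in treated women would pass about 97% of the time, or about 87% with 364 per arm. With the planned cross-over added to 568 per arm, it would pass more than 99.9% of the time.

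It would go too far to conclude that equivalence is close to automatic. With half the women untreated and no cross-over, a 1.5-point difference passes about 48% of the time and a 2.0-point difference only about 2.5%. The 86.5% at 2.0 points requires the cross-over as well.

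The figures assume a time-averaged AUC on the 10-point scale (a raw area has no 1.0-point margin), SD 2.2 throughout, 1:1 allocation, no arm difference among untreated women, and a 95% CI rule. Section 8.1 states no such rule and names the Mann-Whitney test for continuous variables.

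**What to change.** 1. Reconcile 8.1 with 4.4 by naming one decisive comparison: women who requested pain relief, analysed by allocated arm, from the request onwards, using a time-averaged AUC.
2. Keep the all-randomised, whole-labour intention-to-treat analysis alongside it.
3. Because cross-over alone leaves about 58% false equivalence at the margin in that set, claim equivalence only if the per-protocol analysis also lies within the margin. Define that set as women treated as allocated. Requiring the all-randomised interval as well adds no protection against dilution, since that analysis is the more diluted one.
4. State whether the low-risk women are part of the 1136.

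The cost is wording and some reporting. Section 8.1 already records the time from request to start of analgesia, so little or no new data should be needed. The real price is that requesting is a choice made after randomisation with the allocation known, and the per-protocol set is selected too. Report request rates and the baseline characteristics of requesters by arm. Adjusting for centre and parity helps but does not fully remove this selection.
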